### 2.7 Blinding

We will implement a three-way separation of efficacy evaluators, acupuncture operators, and statisticians. Because the control group uses sham acupuncture, it is possible to blind the subjects. Blinding will be assessed after the last treatment using a questionnaire that asks participants if they were in the real treatment group or the sham treatment group, with possible responses of “real treatment group,” “sham group,” or “do not know.”

### 2.8 Intervention

All practitioners in this trial are licensed traditional Chinese medicine acupuncture therapists with at least 5 years of clinical experience, and they will be trained to master the study protocol. The acupuncturist will be asked to administer the standard manipulation for treatment.

### 2.9 Treatment group

The acupuncture group acupoints used will be Baihui, Yintang, Hegu, Taichong, Neiguan, and Shenmen. After routine skin disinfection, the adhesive pad and plastic guide base of the Park acupuncture needle device will be attached to the skin surface. An acupuncture needle with a diameter of 0.35 mm and a length of 25 mm will be placed inside the plastic guide, and it will be inserted into the skin along the direction of the guide. There will be no lifting or twisting manipulations performed after the needle is inserted into the acupuncture point. The selection of acupuncture points will follow the standards outlined in the National Standard of the People's Republic of China, titled “Names and Locations of Acupoints” (GB/T 12346-2006).

### 2.10 Sham acupuncture group

The acupoints for the sham group will be the same as those in the acupuncture group. After routine skin disinfection, the adhesive pad and plastic guide base of the Park acupuncture needle device will be attached to the skin surface. An acupuncture needle with a diameter of 0.40 mm and a length of 25 mm will be placed inside the plastic guide. Light tapping or pressure techniques will be applied without penetrating the skin.

### 2.11 Health control group

Healthy controls and patients were included at a 1:2 ratio. The healthy control group will not receive any intervention. They will maintain normal work and rest times. During the baseline period, the same scales and cognitive function assessments were conducted as those performed on the patients. For the trial work plan, see Figure 2.

**Figure 2 F2:**
[figure not shown]
Trial work plan. The main outcome measure is HAMA. The remaining outcome measures are the secondary outcomes of the study.

### 2.12 Outcomes

Since the HAMA is essentially related to the purpose of the study, it is an observation index that can accurately reflect the effectiveness of acupuncture and is a recognized evaluation standard in anxiety research. Therefore, this trial adopted the HAMA as the primary outcome indicator. In order to evaluate the degree of anxiety and symptoms of the participants from multiple dimensions and analyze the differences between subjective and objective assessments, this study added secondary outcome indicators. When the primary outcome indicator has statistical significance, the statistical analysis results of the secondary outcome indicators are of reference value.

#### 2.12.1 Primary outcome

The primary outcome measure will be the Hamilton Anxiety Rating Scale (HAMA). Developed by psychiatrist Max Hamilton in 1959, HAMA aims to provide a quantified and standardized method for assessing anxiety symptoms (33). It was one of the first scales in the field of mental health and continues to be widely utilized. HAMA consists of 14 items, each targeting different anxiety symptoms or signs. These items include emotional anxiety, somatic anxiety, insomnia, intellectual functioning, somatic symptoms, behavioral symptoms, fear of illness, psychological symptoms, reproductive symptoms, gastrointestinal symptoms, respiratory symptoms, cardiovascular symptoms, muscle symptoms, and sensory organ symptoms. Scores for each item range from 0 (no symptoms) to 4 (severe symptoms). The total score ranges from 0 to 56 points. Higher scores indicate more severe anxiety symptoms. A score > 17 indicates mild anxiety, while scores between 25 and 30 are considered moderate to severe anxiety (34). HAMA is used not only in clinical assessments, but also in research settings to evaluate the effectiveness of drug treatments, to monitor changes in anxiety symptoms, or to serve as a diagnostic tool. HAMA is thus a comprehensive and complex tool for assessing and monitoring anxiety symptoms in adults. The reliability and validity of HAMA are adequate (Cronbach's alpha is 0.921, and validity is 0.529–0.727) (35, 36). With wide applications in both clinical and research environments, it has become one of the standard tools in the field of mental health.

#### 2.12.2 Secondary outcomes

The Sleep Deprivation Index (SDI) is used to assess the extent of sleep deprivation in patients. It is a useful tool for quantifying and evaluating a person's level of sleep deprivation. The SDI primarily collects data on the difference between average weekend sleep duration and average weekday sleep duration, represented numerically (37). The content of the SDI includes responses to the following questions: (a) In the past 2 weeks, how many hours did you sleep on average on weekdays? b) On weekends, if no one wakes you up, how many hours do you sleep on average? By collecting data on the Sleep Deprivation Index, the degree of sleep deprivation in participants can be observed to assess its correlation with anxiety status.

The Epworth Sleepiness Scale (ESS) is used to assess daytime sleepiness. The ESS is a widely used questionnaire developed by Australian sleep expert [name] in 1991 (38). The ESS consists of eight items, each describing typical situations in daily life and requiring respondents to assess the likelihood of falling asleep in these situations. Each item is scored on a range from 0 to 3 points: 0, never doze; 1, slight chance of dozing; 2, moderate chance of dozing; 3, high chance of dozing. The total score ranges from 0 to 24, with higher scores indicating greater daytime sleepiness. The interpretation of total scores is as follows: 0–5, normal daytime alertness; 6–10, normal range of sleepiness; 11–12, mild sleepiness; 13–15, moderate sleepiness; 16–24, severe sleepiness (38). The ESS is mainly used for the diagnosis and assessment of disorders related to excessive daytime sleepiness, such as obstructive sleep apnea and narcolepsy. It can also be used to assess the effectiveness of treatments or as a research tool. The ESS's internal consistency is generally considered good, with Cronbach's alpha coefficients typically ranging from 0.7 to 0.9. Some studies have also found that the ESS has good test–retest reliability, indicating relative consistency in scores for the same respondent at different time points (39). The validity of the ESS is widely supported, as its items are based on common daily activities directly related to daytime sleepiness. The correlation between ESS scores and other measures of sleep quality and sleepiness (such as polysomnography) has been confirmed (39).

The State-Trait Anxiety Inventory (STAI) is a psychological measurement tool used to assess an individual's level of anxiety. Developed by American psychologist Charles Spielberger and his colleagues in the 1970s, it is widely used in clinical and research settings (40). The STAI consists of two independent scales, measuring state anxiety and trait anxiety. State anxiety refers to the level of anxiety an individual experiences at a specific moment or in a particular situation. It is a transient emotional experience related to a specific context. The state anxiety portion of the STAI includes 20 items that ask participants to describe their current feelings. Trait anxiety refers to an individual's general and stable tendency toward anxiety, reflecting their overall reaction to threats and dangers. The trait anxiety portion of the STAI also consists of 20 items, asking participants to describe their usual feelings. Each item on the STAI is scored on a four-point scale, ranging from “almost never” to “very much,” with varying degrees of consistency. The total score for each scale ranges from 20 to 80, with higher scores indicating a higher level of anxiety. The STAI can be used for individuals of different ages and backgrounds, including children, adolescents, and adults. It has widespread applications in clinical assessment, research, and educational environments, used for diagnosing anxiety disorders, evaluating treatment outcomes, and studying the relationship between anxiety and other variables (41). The internal consistency reliability of the STAI is typically high, with Cronbach's alpha values ranging from 0.86 to 0.95, indicating high consistency among questionnaire items. The test–retest reliability of the STAI has also been demonstrated to be reliable. Some studies have found that the test–retest reliability of the Trait Anxiety Scale ranges from 0.65 to 0.75, while that of the State Anxiety Scale ranges from 0.16 to 0.62. This suggests that the Trait Anxiety Scale has higher stability, while the State Anxiety Scale is more influenced by specific situations. The content validity of the STAI is widely recognized, as it covers multiple aspects of anxiety, including physiological, cognitive, and emotional components. Through factor analysis, researchers have demonstrated that the two STAI subscales (state and trait anxiety) are independent, supporting its structural validity (41). The STAI shows a high correlation with other anxiety measurement tools, such as the Taylor Manifest Anxiety Scale, further validating its standard effectiveness (42).

The Self-Rating Anxiety Scale (SAS) is a self-assessment tool designed to evaluate an individual's level of anxiety, with the aim of quantitatively assessing the patient's anxiety status in a clinical setting (43). The SAS employs a four-point scoring system, primarily assessing the frequency of symptom occurrence. Among the 20 items, 15 are framed with negative wording and scored on a scale from 1 to 4 as described above. The remaining five items (5, 9, 13, 17, 19) are presented with positive wording and scored in reverse order from 4 to 1. According to the standard scores based on Chinese norms, the cutoff values for SAS are set at 50 points, with scores ranging from 50 to 59 indicating mild anxiety, 60–69 indicating moderate anxiety, and scores above 70 indicating severe anxiety. Raw scale scores for the SAS range from 20 to 80, with satisfactory psychometric characteristics that include internal consistency (Cronbach's alpha = 0.82) and concurrent validity (*r* = 0.30 with the Taylor Manifest Anxiety Scale) (43, 44).

Event-Related Potentials (ERPs) will also be used as a secondary outcome. The study will employ the PVT, ANT, and Go/No-go emotional detection paradigm to observe differences in the P300, N100, N200, P200, and other EEG changes related to participants' psychomotor vigilance, attention network effects, and emotional attention bias.

The PVT is a neuropsychological test designed to measure an individual's vigilance and reaction time (45). It is widely used in research on and the assessment of cognitive function changes related to sleep deprivation, work stress, medications, and other factors. The PVT is typically a simple visual reaction time task where participants need to respond as quickly as possible to randomly presented visual stimuli, often a numerical timer starting from 0. The time from stimulus onset to the participant pressing a button is recorded as reaction time. The PVT can be used to measure various parameters, including average reaction time, fastest and slowest reaction time, standard deviation of reaction time, as well as errors, such as premature button presses or failures to respond. The PVT is an extensively used tool for measuring vigilance and reaction time, capturing the impact of various factors on cognitive function through a straightforward visual reaction task, providing a detailed assessment of participants' attention. PVT measures sustained attention and is used to assess the effect of drowsiness on brain operational efficiency. PVT performance is considered to reflect a person's arousal and attention state and is highly sensitive to drowsiness and sleep deprivation. When sleep deprivation occurs, the amplitude of the P300 wave decreases, and its latency increases. It has also been shown that the P300 latency increases with pre-sleep drowsiness (46). Research has demonstrated that PVT is an effective and reliable indicator that can quantify alertness changes related to sleep restriction over a period of 3 months (47).

The ANT is a cognitive test used to measure and evaluate the functionality of attention networks. Developed by Michael I. Posner and other researchers, the ANT is designed to study how people control attention and process information. The ANT combines measurements of different types of attention, including alerting, orienting, and executive control (48). The ANT is based on three main attention networks: alerting network, orienting network, and executive control network. It typically consists of a series of rapidly presented visual stimuli, requiring participants to respond as quickly and accurately as possible. The key components of the test include central arrows, peripheral arrows, and cue stimuli. By analyzing participants' reaction time and accuracy, the ANT can measure parameters such as alerting effects, orienting effects, and conflict effects. The ANT is a tool for measuring and understanding various aspects of attention and finds widespread applications in cognitive science, clinical psychology, developmental psychology, and other fields (49). Patients with anxiety often exhibit symptoms of decreased attention. Various prolonged workloads can deplete attentional resources. ERP studies on sustained attention and vigilance contribute to understanding the brain mechanisms that support and maintain prolonged attention and vigilance (50). The research on mental fatigue using various tasks generally shows that with extended performance, the amplitudes of multiple ERP components, including N100 and P300, decrease (51). In studies of sustained attention, N100 is associated with the early stages of selective attention to task stimuli, while P300 is an indicator of the later stages of conscious stimulus evaluation and classification (52). Relevant research indicates that the Attention Network Test (ANT) demonstrates high reliability in execution in clinical use but low reliability in alerting and orienting scores (48, 53).

In Go/No-go emotional detection, emotional attention bias refers to an individual's tendency when processing emotional information, especially when emotional information competes for attention with other non-emotional information (54). The Go/No-go emotional detection paradigm is an experimental method used to study emotional attention bias, and related ERPs provide insight into how the brain processes this information (55). In the Go/No-go task, participants are instructed to respond to specific types of stimuli (e.g., speech or faces with specific emotions) and withhold responses to other types of stimuli. This paradigm can be used to study attention and response control to different emotional stimuli. Patients with anxiety often exhibit impaired cognitive control and avoidance behaviors. Inhibitory control is an important component of the cognitive control system, and studies suggest that the inability to inhibit responses to negative stimuli is related to anxiety. The N2 component in emotion-related GO/No-go tasks is associated with conflict monitoring processes, while the P3 component is more related to conflict resolution and behavioral inhibition (56). In a previous study that involved an emotion-related GO/No-go task, anxious patients showed reduced amplitude differences at the N2 stage when required to inhibit facial stimuli. The GO/No-go amplitude for neutral faces predicted self-reported anxiety levels (57). These results suggest that dysfunctional inhibitory control may be a characteristic marker of anxiety related to a decreased conflict monitoring ability or decreased active inhibition capacity.

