## 1 Introduction

### 1.1 Partial sleep deprivation leads to anxiety disorders in early adulthood

The National Sleep Foundation defines partial sleep deprivation (PSD) in early adulthood as sleeping < 6 h (1). Sleep and mood are closely related, and studies have shown that sleep deprivation is associated with increased physiological arousal, decreased ability to experience positive emotions, and increased sensitivity to negative emotional experiences (2). Sleep disorders are a major predictor of anxiety attacks (3), and they are also responsible for the onset of anxiety symptoms and the worsening of baseline anxiety states. A study of sleep conditions and anxiety states showed that naturally occurring partial sleep deprivation in school students led to increased levels of self-reported anxious arousal symptoms the next day (4). Naturalistic studies of the relationship between sleep and mood experiences in non-clinical samples have also shown that shorter sleep duration is typically associated with increased negative mood and anxiety and depressive symptoms the next day (5).

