### 1.4 Objectives

This study aims to observe participants with comorbid GAD and PSD to explore the intrinsic brain cognitive mechanisms associated with naturally occurring PSD in conjunction with GAD. Furthermore, the study seeks to investigate the clinical effects of acupuncture on improving both sleep deprivation and GAD symptoms in this comorbid population.

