### 2.3 Inclusion criteria

The inclusion criteria are as follows:

1) Between 18 and 25 years of age.2) An average sleep duration equal to or < 6 h per night in the past 30 days.3) A score of ≥5 points on the 7-item Generalized Anxiety Disorder Scale (GAD-7).4) No anti-anxiety or insomnia-related medications taken or acupuncture treatments for anxiety or insomnia received in the most recent 30 days.5) Willingness to participate in the clinical study and sign an informed consent form.

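### The only outcome for the extent of sleep deprivation is a weekend-weekday difference, so it cannot show whether participants sleep longer, although the trial defines sleep deprivation by hours slept

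*Protocol article*

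**What the plan says.** The Introduction (section 1.1) cites a definition by hours slept: it "defines partial sleep deprivation (PSD) in early adulthood as sleeping < 6 h". Section 2.3 recruits on the same kind of quantity: "An average sleep duration equal to or < 6 h per night in the past 30 days". Sections 2.1 and 2.2 repeat the 6 h limit. Section 1.4 makes sleep part of the clinical aim, which is to "investigate the clinical effects of acupuncture on improving both sleep deprivation and GAD symptoms in this comorbid population".

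Section 2.12.2 then assigns the measurement of sleep deprivation to one index: "The Sleep Deprivation Index (SDI) is used to assess the extent of sleep deprivation in patients". It defines the index in these words: "The SDI primarily collects data on the difference between average weekend sleep duration and average weekday sleep duration, represented numerically". Two questions feed it. The first is "In the past 2 weeks, how many hours did you sleep on average on weekdays". The second is "On weekends, if no one wakes you up, how many hours do you sleep on average"; it is conditional and has no recall window of its own. The section also plans to relate the index to anxiety status.

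No listed outcome is sleep duration. The Epworth scale covers daytime sleepiness, and insomnia is one of the 14 HAMA items.

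**The concern.** The quantity used to define and enrol the population is a level (hours per night). The quantity used to judge whether it improved is a contrast between two levels. A contrast discards whatever the two levels share, so a change common to weekdays and weekends is invisible to it.

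What is at stake is the sleep-deprivation part of the objective. A null SDI result could hide a real gain in sleep, and a lower SDI could arise without one. A correlation of SDI with anxiety would describe the weekend-weekday gap, not short sleep. Healthy controls complete the same scales at baseline (section 2.11), and there too the index need not separate a short sleeper from a normal one.

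**Working it through.** **No figure to reproduce.** The protocol gives no SDI effect size, standard deviation, power or cut-off. The check is of the definition.

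**Inputs.** From section 2.12.2: W = average weekday hours (first question) and E = average unrestricted weekend hours (second question). I take SDI = E − W, following the order in which the difference is written, so a lower value means less deprivation. For comparison, average sleep is M = (5W + 2E)/7. In the worked cases and the correlations below, E is treated as if it were actual weekend sleep. The hours are assumptions for illustration.

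**Step 1, algebra.** For an equal gain g on all nights, SDI = (E + g) − (W + g) = E − W. The change is 0 whatever the size of g. This needs no assumed hours.

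**Step 2, level.** For 5 h/5 h, SDI = 5 − 5 = 0 and M = 5.0 h, which meets the entry limit. For 8 h/8 h, SDI = 8 − 8 = 0 and M = 8.0 h. The index does not distinguish them.

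**Step 3, worked cases.** Assumed baseline W = 5, E = 8: M = (25 + 16)/7 = 5.86 h (meets the limit), SDI = 3.

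| Change | W/E after | Change in M | Change in SDI | Change in W |
|---|---|---|---|---|
| +1 h weekdays only | 6/8 | +0.71 h | −1 (better) | +1 |
| +1 h every night | 6/9 | +1.00 h | 0 | +1 |
| Weekday +0.5 h, weekend +1.5 h | 5.5/9.5 | +0.79 h | +1 (worse) | +0.5 |
| Weekend −1 h only | 5/7 | −0.29 h | −1 (better) | 0 |
| Weekday −0.5 h, weekend −1.5 h | 4.5/6.5 | −0.79 h | −1 (better) | −0.5 |

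The SDI has the right sign in the first row only. Weekday hours alone have the right sign in four rows and show no change in the weekend-only row.

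**Step 4, how closely the two move together.** Let the weekday and weekend changes have equal standard deviations and correlation ρ. Then corr(ΔSDI, ΔM) = −3(1 − ρ)/√[2(1 − ρ)(29 + 20ρ)]. A faithful index would give −1.

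- ρ = 0: −3/√58 = −0.39
- ρ = 0.3: −2.1/√49 = −0.30
- ρ = 0.5: −1.5/√39 = −0.24
- ρ = 0.8: −0.6/√18 = −0.14

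If the weekend change has half the standard deviation of the weekday change, the formula becomes (−0.643 + 0.214ρ)/√[(1.25 − ρ)(26 + 10ρ)/49]. It lies between about −0.77 and −0.84 for ρ from 0 to 0.8. If the weekend answer does not change at all, it is −1. How well the SDI follows sleep duration thus depends on how much the weekend answer moves, which the protocol does not state.

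**Step 5, recall window.** The weekday question covers 2 weeks. The abstract gives evaluations at 0, 1 and 2 weeks. If the question is asked at week 1, about one of its two weeks precedes treatment. With an immediate, constant effect and equally weighted recall, the reported weekday change would be about half the true one. At week 2 the window matches the treatment period.

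**The case against.** The strongest defence is that the SDI is a sleep-debt measure. The second question asks about unrestricted sleep and may stand for sleep need. Need minus weekday sleep is then a coherent reading of deprivation, and a 5 h/5 h score of 0 is a choice of construct. The source cited for the index is not at hand, so its validity as a debt measure is not judged here. The defence stands that far, but it does not close the gap with the protocol's own definition, which is hours slept and not hours short of need.

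If unrestricted weekend sleep is fairly stable over a few weeks, the SDI falls hour for hour with weekday gain. This also stands. A reader might infer from the table that the SDI runs backwards, so that an effective treatment should be expected to look harmful. The documents do not support this. All the correlations in step 4 have the correct sign; reversal is possible in particular patterns but is not shown to be the expected group effect.

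A reader might also infer that the trial has no other evidence on sleep loss. That is too strong: the psychomotor vigilance test is described as highly sensitive to sleep deprivation, and the Epworth scale and the HAMA insomnia item bear on sleep. None of them measures duration.

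The week-1 point is conditional. Which instrument is given at which visit is set out in a figure that is not shown.

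Finally, the SDI is secondary, section 2.12 gives secondary results reference value only when HAMA is significant, and weekday hours are already collected. This limits the damage and makes the repair easy, but neither weekday hours nor any other duration is named as an outcome.

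**Conclusion.** The point holds in limited form. By its printed definition the SDI is unaffected by any equal change across nights and does not encode the level of sleep. Neither a null nor a positive SDI result, nor its correlation with anxiety, can therefore be read as evidence about sleep duration, the quantity on which participants are recruited. This much follows from algebra and the protocol's own wording.

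The size of the problem in practice is open. It ranges from none, if unrestricted weekend sleep stays fixed, to a correlation of only −0.14 to −0.39 with change in average sleep, if weekend and weekday changes vary equally. These figures rest on assumed variances and correlations. The primary HAMA comparison is not affected.

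**What to change.** Name reported weekday sleep duration, the first SDI question, as the secondary outcome for sleep deprivation. Keep the SDI as a descriptive measure of the weekend-weekday gap, and use weekday hours in the planned correlation with anxiety.

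The weighted mean (5W + 2E)/7 may be reported as a supportive summary only. The second question asks about unrestricted sleep with no stated window, so the mean is not actual nightly duration.

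If the weekday question is given at week 1, either ask about the past week at post-baseline visits or do not test the item at week 1.

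The cost is one sentence on the outcome and, if needed, one recall phrase on the case report form; no new items or visits are required. There are two small downsides: weekday duration leaves out weekend sleep, and a changed recall phrase departs from the cited wording of the index.
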